### Randomization and group allocation

Once eligibility is confirmed during screening, participants are randomly assigned to the intervention or the comparison group in a 1:1 ratio by an independent researcher using computer-generated randomization sequences with stratified block randomization by age (12 to 15 years / 16 to 25 years). Staff will not be blind to group allocation. Participants are blind to their allocated group during Wave 1 assessment. The nature of the intervention precludes concealment from participants and staff. Recruitment and retention in the trial will be maximized via study-specific training of RA’s and weekly staff-meetings to discuss the progress of the trial. In addition, retention was considered in great detail when designing the study by integrating input from young people with lived experience with mental-ill health, conducting a feasibility study and integrating recommended adjustments to increase compliance, and implementing insights from earlier ESM-studies.

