### Data analysis plan and power calculations

Analyses that cover effectiveness of PRIMARY will be performed according to a modified version of the *intention-to-treat* principle [71], which entails including all participants with at least one data point post-baseline regardless of their compliance during the study. This way, random selection in the sample will be guaranteed which ensures the most accurate conclusions following the analyses. In the following section, analyses will be outlined for each study objective (i.e., research question) as well as the required sample size to answer the research questions based on relevant power analyses and recent literature^1^. Multiple imputation will be considered if the amount of missing values is non-trivial. The randomization stratification variable of age and gender will be examined as covariates in the analyses described below. Other covariates, such as concomitant treatment, will also be considered.

To examine the effectiveness of PRIMARY, an ANCOVA-test will be used to compare data from Wave 1 and 2 by study group (study objective 1). Specifically, the following variables will be examined: emotion regulation, quality of relationships, and self-harm. To reach a power of 0.80, the power analyses run in G*Power 3.1 [72]^2^ and R [73], with an additional correction for the pre-test as a covariate, indicated a sample size of *n* = 48 per group to be necessary to detect a medium effect size (α = 0.05). Taking into account a drop-out of 10% (based on the feasibility study), a total sample size of *N* = 106 is necessary to answer this research question.

Regarding the effect of PRIMARY on the effectiveness of subsequent specialized treatment (i.e., HYPE), an ANOVA-test repeated measures with a within-between interaction will be applied to Wave 1, 2 and 3 including only those participants receiving HYPE treatment (study objective 2). To reach a power of 0.80, a sample size of *N* = 42-106 is necessary when considering a medium-large effect size (G*Power 3.1) [72]^1^. Taking into account the 10% drop-out from the feasibility study, a sample size of *N* = 46-118 is required (i.e., young people receiving HYPE treatment).

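### Objective 2 uses the Wave 1 score as an outcome level where objective 1 uses it as a covariate: a valid test, but less efficient for the omnibus interaction and for contrasts anchored on Wave 1

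*Protocol article*

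**What the plan says.** All points here are in the protocol article, Data analysis plan and power calculations, unless stated otherwise.

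- **Objective 1** compares the arms by ANCOVA on Waves 1 and 2. Its sample size was computed "with an additional correction for the pre-test as a covariate".
- **Objective 2** uses a different model: "an ANOVA-test repeated measures with a within-between interaction will be applied to Wave 1, 2 and 3 including only those participants receiving HYPE treatment". Its size statement is that "a sample size of *N* = 42-106 is necessary when considering a medium-large effect size", at a power of 0.80. With 10% drop-out this becomes 46 to 118. The text gives neither a numerical effect size nor a correlation for objective 2.
- **Covariates** for all analyses are age, gender and possibly others such as concomitant treatment. The Wave 1 score is not named as a covariate for objective 2.
- **Timing.** Under Measures, Wave 1 precedes the intervention in everyone. Under HYPE, treatment starts after Wave 2 and clinicians independent of the study decide who enters it.
- **Contrasts.** Under Objectives, Wave 3 is to be compared both with Wave 1 and with Wave 2.

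**The concern.** PRIMARY cannot affect a score taken before it starts. When that score is an outcome level, the interaction compares the arms partly on raw change from Wave 1, which carries the full noise of the baseline measurement. When it is a covariate, only the part of the later scores that Wave 1 does not predict remains as noise.

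The protocol claims this gain for objective 1 and forgoes it for objective 2, whose planning range starts at 42 participants and whose final number depends on clinical referral to HYPE. With 21 per arm, chance alone gives a Wave 1 difference between arms with a standard deviation of √(2/21) = 0.31 SD. A change comparison passes a fraction 1 − ρ of that difference into the result, which is half of it at ρ = 0.5. At stake is power, and with it the width of the interval, in the nested HYPE comparison.

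**Working it through.** **Inputs.** From the protocol: 48 per group for objective 1; N = 42 to 106 for objective 2; power 0.80; α = 0.05 (stated for objective 1, assumed for objective 2); 1:1 allocation at randomisation, assumed to carry over to the HYPE subset. Assumed: equal variances and the same correlation ρ between every pair of waves, with ρ = 0.5 and a range of 0.3 to 0.7.

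**1. Reproduce the plan's figures.**
- Objective 1: n per group = 2(1.96 + 0.84)²(1 − ρ²)/d². With d = 0.5 this gives 62.8, so 63, without the covariate. With ρ = 0.5 it gives 62.8 × 0.75 = 47.1, so 48, as stated.
- Objective 2: λ = f²·N·3/(1 − ρ), on 2 and 2(N − 2) df. At ρ = 0.5, f = 0.20 and N = 42 give λ = 10.08 and power 0.803; f = 0.125 and N = 106 give λ = 9.94 and power 0.807. Both stated sizes are reproduced.
- The f values were found by search. N fixes only f²/(1 − ρ), so ρ = 0.5 is consistent with objective 2 but not proved by it. It is also the value that objective 1 implies if medium means d = 0.5.

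**2. Information under the two models at ρ = 0.5.** Write the arm effect at Waves 1, 2 and 3 as (0, δ₂, δ₃).
- Planned interaction: λ = (N/4)·Σ(δ − mean δ)²/(1 − ρ).
- Adjusted for Wave 1: the conditional variance of each later score is 1 − ρ² = 0.75 and their covariance is ρ(1 − ρ) = 0.25. Inverting that matrix gives λ = (N/4)·(1.5δ₂² + 1.5δ₃² − δ₂δ₃).

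| Arm effect | Planned λ ÷ (N/4) | Adjusted λ ÷ (N/4) | Ratio |
|---|---|---|---|
| Wave 3 only (0, 0, d) | 1.333d² | 1.5d² | 1.125 |
| Builds up (0, d/2, d) | 1.0d² | 1.375d² | 1.375 |
| From Wave 2 (0, d, d) | 1.333d² | 2.0d² | 1.5 |

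**3. Power.** At N = 42 the planned test reaches 0.80 at λ = 10.00. Multiplying by the ratios gives λ = 11.26, 13.76 and 15.01. On 2 and 78 df the joint test has power **0.847, 0.913 and 0.935**. At N = 106 the results agree to within 0.001. ANCOVA of Wave 3 alone at N = 42 gives 0.870, 0.945 and 0.870.

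**4. Sensitivity.**
- Over ρ = 0.3 to 0.7 and the three patterns, the joint test ranges from 0.82 to 0.98.
- In a simulation at N = 42 and ρ = 0.5 (8,000 runs per pattern), the planned test gave 0.796 to 0.804. A joint test with unstructured covariance gave 0.819, 0.899 and 0.920, a gain of about 2 to 12 points.
- With f = 0.25 the planned test already has power 0.946 at N = 42, and with f = 0.40 practically 1. At most about 5 points remain to be gained.
- For a single Wave 3 minus Wave 1 contrast, the variance falls from 2(1 − ρ) to 1 − ρ², a factor (1 + ρ)/2 = 0.75. Power rises from 0.80 to about 0.90 (0.94 at ρ = 0.3, 0.86 at ρ = 0.7).
- For Wave 3 minus Wave 2, the covariance with Wave 1 is ρ − ρ = 0, so the variance ratio is exactly 1. If correlations decay as ρ and ρ², the ratio is 1 − (ρ² − ρ)²/[2(1 − ρ)], or 0.97, 0.94 and 0.93 at ρ = 0.3, 0.5 and 0.7.
- Testing the average of Waves 2 and 3 has power of only about 0.47 if the effect appears only at Wave 3.

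**The case against.** The strongest reply is that nothing here is an error. The within-between interaction is a standard, valid test, and the stated N was computed for that test. This stands.

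Three further points also stand:
- The upper end of the gain needs an arm effect already present at Wave 2, which is what objective 1 tests. For an effect that arises during HYPE the gain is about 5 points, or about 2 with an unstructured covariance.
- The effect size and correlation for objective 2 are not stated, so every figure is conditional on assumptions.
- The HYPE subset is formed by clinicians after Wave 2, so the usual argument for ANCOVA in a fully randomised comparison does not carry over whole. Where the arms differ stably at Wave 1, adjusted and change-score analyses can disagree, and the adjusted one is not automatically the unbiased one.

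A reader might infer that the gain holds for whichever wave contrast objective 2 finally tests. It does not: the Wave 3 versus Wave 2 comparison named under Objectives gains essentially nothing. A reader might also infer that adjustment cures imbalance from selection into HYPE. It deals with chance imbalance at Wave 1 only.

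The reply does not show that the planned model is preferable for the omnibus test. In every pattern examined, the adjusted joint test had more power than the planned interaction.

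**Conclusion.** The point holds as an efficiency improvement worth making, not as a flaw that invalidates objective 2. The documents do not support a claim that the objective is biased by this choice or undersized for its planned test. At ρ = 0.5 with equal correlations, the planned interaction gives up about 5 to 14 points of power, depending on when the effect appears. That loss applies to the omnibus interaction and to contrasts anchored on Wave 1. It shrinks with a higher correlation, an unstructured covariance or a larger true effect.

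**What to change.** For the between-arm comparison in objective 2:
- Model the Wave 2 and Wave 3 scores as outcomes. Use the Wave 1 score of the same measure and the age stratum as covariates, with arm, wave and arm-by-wave terms.
- Test the arm effect jointly over Waves 2 and 3 (2 df), or at Wave 3, and name the choice in advance. Do not test the average of the two waves. The arm-by-wave term alone is the Wave 3 versus Wave 2 contrast and brings no gain.
- Report the arm effect as a Wave 1-adjusted difference, and report within-arm change from Wave 1 descriptively so that the comparison promised under Objectives is kept.
- State the effect size and correlation assumed for objective 2.

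The cost is wording in the analysis plan, with no new data or participants. Data collection is predicted to run until April 2026 (Trial status), so the change should be fixed before the analysis. The downsides are that the effect is read as a baseline-adjusted difference rather than as raw change, that a linear relation with Wave 1 is assumed, and that selection into HYPE after randomisation remains and should be stated as a limitation.

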### Objectives

The first objective of this RCT is to determine whether PRIMARY, compared to a waiting list control, is effective in improving the following outcomes: self-harm, emotion regulation, and quality of relationships. To this end scores at baseline (Wave 1) and at the end of the intervention phase (Wave 2) will be compared. The second objective is to examine the effectiveness of PRIMARY combined with subsequent specialized treatment in the early intervention program Helping Young People Early (HYPE) [41] in improving the outcomes for young people with borderline personality pathology. Scores on the specified outcome variables after 10 weeks of HYPE treatment (Wave 3) will be compared to scores at baseline (Wave 1) and at the end of the intervention phase (Wave 2) for participants who attended HYPE. The third objective is to investigate the associations between emotions, relational support and conflict, adaptive coping strategies, and self-harm using individual-level ESM data. The fourth objective is to examine the participants’ and clinicians’ satisfaction regarding the use of PRIMARY. This will be examined at the end of the intervention phase (Wave 2).

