## Methods

### Design

To facilitate transparency, the current protocol paper was written in accordance with the SPIRIT guidelines [42]. The SPIRIT Checklist is provided in the Supplemental Material.

This study is a multicenter, parallel groups, randomized controlled trial of the PRIMARY intervention compared with a waiting list control in outpatients aged 12 to 25 years (inclusive). The study also includes a nested evaluation of the effect of PRIMARY on the effectiveness of subsequent specialized treatment (HYPE) [41].

The design of the PRIMARY study was co-created by clinicians, young people with lived experience of mental ill-health, and researchers to ensure it is acceptable to all. For example, young people with lived experience provided feedback on how to adapt the ESM lay-out and script for the weekly report sessions to appeal to their age group. To guarantee the intervention is easy-to-implement, it is constructed to be delivered by research assistants (RA’s) rather than clinicians. RA’s hold a bachelor’s diploma in psychology or a related field and completed a suicide prevention e-learning module. Adherence to the prescribed PRIMARY intervention is promoted via detailed study procedures and scripts, as well as routine joint appointments with the RA, participant and AA or [name]. All individual participant data (i.e., questionnaires and weekly, graphical reports) are made available within the electronic patient record of the participant. This is a direct benefit of participation in the study for the participant, as this information can be integrated into their diagnostic or treatment process by their clinician.

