### HYPE

After finishing the assessment at the end of the study intervention phase (i.e. Wave 2), it is anticipated that participants in an early stage of BPD (i.e., ≥ three BPD criteria) will receive specialized treatment called HYPE (Helping Young People Early) [41]. Allocation to HYPE is determined by clinicians independent from the study. HYPE is a time-limited integrative treatment program based on the principles of Cognitive Analytic Therapy (CAT). The time-limit comprises 16 individual, weekly psychotherapy sessions, supplemented with psychiatric, psychosocial and family sessions if indicated. There is a follow-up period of six months, wherein the young person can schedule up to four sessions.

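### The three-wave group-by-time interaction for objective 2 includes PRIMARY's own pre-HYPE effect, so it does not isolate a change in the effect of HYPE

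*Protocol article*

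**What the plan says.** The article words objective 2 in two ways.

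- Objectives: "The second objective is to examine the effectiveness of PRIMARY combined with subsequent specialized treatment". The next sentence says that Wave 3 scores "will be compared to scores at baseline (Wave 1) and at the end of the intervention phase (Wave 2) for participants who attended HYPE". It does not say that these comparisons are made between the arms.
- Design: the trial includes "a nested evaluation of the effect of PRIMARY on the effectiveness of subsequent specialized treatment (HYPE"). The analysis section uses the same idea: "Regarding the effect of PRIMARY on the effectiveness of subsequent specialized treatment (i.e., HYPE").

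One test is named, in Data analysis plan and power calculations: "an ANOVA-test repeated measures with a within-between interaction will be applied to Wave 1, 2 and 3", limited to those who receive HYPE. The sample size is attached to this test: power 0.80, N = 42 to 106 for a medium to large effect, and 46 to 118 after 10% dropout.

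The HYPE section places the start of HYPE at the point "After finishing the assessment at the end of the study intervention phase (i.e. Wave 2"). Under Measures, Wave 3 falls 10 weeks after HYPE begins. The Wave 1 to Wave 2 comparison by arm is already the objective 1 analysis.

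**The concern.** Whether PRIMARY alters the benefit of HYPE is a question about the interval in which HYPE is given, Wave 2 to Wave 3. The interaction over three waves also counts the interval before HYPE begins. If PRIMARY does what objective 1 hopes for, the arms have already separated at Wave 2, and the interaction is non-null whatever HYPE then does.

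A significant result could therefore be reported as PRIMARY enhancing HYPE when the early gain had merely persisted, or had disappeared. The stated sample size is also tied to a quantity that is not the one asked about. For the Objectives wording, including the early effect is not in itself an error, but the omnibus test does not isolate the arm difference at Wave 3 either.

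**Working it through.** **Inputs from the article.** Two arms, 1:1 allocation, three waves, power 0.80, N = 42 to 106 before dropout. Alpha 0.05 is stated for objective 1; none is stated for objective 2.

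**Assumptions, not in the article.** Compound symmetry; correlation between waves (rho) 0.3 to 0.7; outcome SD of 1; standardised arm differences of 0.3 to 0.8; f = 0.40 (large) and 0.25 (medium).

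**1. The stated N.** Noncentral-F sizing of the interaction at alpha 0.05 gives, for f = 0.40 and 0.25:

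- G*Power default convention, rho 0.5: N = 12 and 28
- Cohen convention: N = 32 and 80
- SPSS convention: N = 34 and 82

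None of these is 42 to 106. With an assumed alpha of 0.05/3, the Cohen convention gives 42 and 104 and the SPSS convention 44 and 106, which is close. Other combinations come as close: a between-subjects test over three measurements at alpha 0.05 and rho 0.7 gives 42 and 104. The settings behind the stated range are therefore not identified, and the calculations below use alpha 0.05 with 0.05/3 as a sensitivity case. Dropout: 42/0.9 = 46.7 (stated 46) and 106/0.9 = 117.8 (stated 118), which is in order.

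**2. What the omnibus test responds to.** With n per arm and arm differences d1, d2, d3 at the three waves, the noncentrality is

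lambda = (n/2) × sum of (dj − mean d)² / (1 − rho), on 2 and 2(N − 2) degrees of freedom.

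Three patterns with different meanings:

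| Arm differences at Waves 1, 2, 3 | Meaning for HYPE | Sum of squares | Simulated rejection, N = 106, rho 0.5 |
|---|---|---|---|
| 0, 0.5, 0.5 | equal effect in both arms | 0.167 | 0.75 |
| 0, 0.5, 0 | smaller gain after PRIMARY, or fading of the early effect | 0.167 | 0.76 |
| 0, 0, 0.5 | larger gain after PRIMARY | 0.167 | 0.76 |

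At N = 106 and rho 0.5, lambda = (53/2) × 0.1667/0.5 = 8.83 in every row. The test has the same power for all three.

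**3. Rejection when HYPE works equally in both arms** (pattern 0, d, d; noncentral F):

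| d | rho | alpha | N = 42 | N = 106 |
|---|---|---|---|---|
| 0.5 | 0.3 | 0.05 | 0.27 | 0.60 |
| 0.5 | 0.5 | 0.05 | 0.36 | 0.76 |
| 0.5 | 0.7 | 0.05 | 0.55 | 0.94 |
| 0.3 | 0.5 | 0.05 | 0.15 | 0.33 |
| 0.8 | 0.5 | 0.05 | 0.75 | 0.99 |
| 0.5 | 0.5 | 0.05/3 | 0.21 | 0.60 |

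In simulation the between-arm contrast of Wave 2 to Wave 3 change rejects at about 5% under this pattern (0.044 to 0.057).

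**4. Power of the change contrast.** The SD of the change is sqrt(2(1 − rho)), which is 1 at rho 0.5. For a 0.5 SD difference in change at two-sided alpha 0.05, a two-sample t-test gives:

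| rho | N = 42 | N = 106 |
|---|---|---|
| 0.3 | 0.27 | 0.58 |
| 0.5 | 0.35 | 0.72 |
| 0.7 | 0.53 | 0.91 |

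For power 0.80 at rho 0.5, n per arm = 2 × (1.96 + 0.84)² × 1/0.25 = 62.7, so 63 per arm and N = 126 before dropout. Across rho 0.3 to 0.7 the total runs from 176 down to 76.

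**5. The contrast has its own limit.** Under the pattern 0, 0.5, 0 the change contrast is also non-null, with power of about 0.72 at N = 106 and rho 0.5. A fading early effect then looks like a weaker HYPE effect.

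**The case against.** The strongest reply is that an interaction test is normally followed by contrasts from the same model, that the Objectives section already mentions Wave 3 against Wave 2, and that a condensed article may leave the contrasts to an analysis plan that is not shown. This stands in part: the three-wave data can answer the question. It does not remove the mismatch, because the article itself attaches one test and one sample size to the question, and the comparisons in Objectives are not stated as between-arm.

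A second reply is that the proposed change contrast is not clean either, since fading makes it non-null. That is correct, and it is why the contrast has to be read beside the Wave 3 difference.

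A third is that the size depends on assumed correlations, effects and alpha. That is also correct, hence the ranges; at alpha 0.05/3 the rejection rates fall to 21% and 60%.

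Two stronger readings should be resisted. A reader might infer that the interaction will be significant whenever PRIMARY works. Only its null hypothesis is false; at N = 42 with a 0.5 SD effect and rho 0.5 the test still misses in about 64% of trials. A reader might also infer that repeated-measures ANOVA, by needing all three waves, contradicts the modified intention-to-treat rule. The same section says that multiple imputation will be considered if missing values are non-trivial, so no contradiction is established.

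**Conclusion.** The concern holds for the omnibus test as the test of objective 2. Its null hypothesis is false whenever PRIMARY has a Wave 2 effect among HYPE recipients, so a significant result does not show that PRIMARY changes the effect of HYPE. For a persisting 0.5 SD effect with HYPE equally effective in both arms, rejection is about 27–55% at N = 42 and 60–94% at N = 106, against the 5% a test of the stated question should give. These figures assume compound symmetry, rho 0.3 to 0.7 and alpha 0.05, none of which the article gives for objective 2. The point that the early effect enters the test needs none of these numbers; it follows from HYPE starting after Wave 2.

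The limitation lies in the named test, not in the data collected. Severity is should-fix: objective 2 is a nested evaluation, and the ANCOVA for objective 1 is not affected.

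**What to change.** 1. Reconcile the Objectives section with the Design and analysis sections, so that objective 2 asks one question or two clearly separate ones.
2. Replace the omnibus interaction as the objective 2 test with named one-degree-of-freedom between-arm contrasts from the same three-wave data. For PRIMARY's influence on the effect of HYPE, use the arm difference in Wave 2 to Wave 3 change. For PRIMARY combined with HYPE, use the arm difference at Wave 3 adjusted for Wave 1.
3. State which contrast leads. Require the change contrast to be interpreted alongside the Wave 3 difference, because fading of the early effect also moves it.
4. Restate power for the lead contrast at the planned N, with its alpha, assumed correlation and effect size, rather than enrolling more. If the change contrast leads, power for a 0.5 SD difference is about 0.35 at N = 42 and 0.72 at N = 106 at rho 0.5.

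The cost is revised wording and one power calculation, with no new data. The downside is a less favourable stated power for the change contrast than the 0.80 now quoted.

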### Data management

Participants fill out the questionnaires through an online portal called ‘RoQua’. At GGz Centraal, RoQua is also used for Routine Outcome Monitoring and it is linked to the electronic patient records. Hence, the answers on the questionnaires of this study are available to clinicians through these records. The data is stored in a secure online environment. RoQua sends personalized links via text messages in which the ESM-questionnaires are embedded. RoQua is formally recognized as an instrument to carry out research in the Netherlands and operates in accordance with the European General Data Protection Regulation [66].

Data will be pseudonymized and stored on a secured network, accessible only by members of the research staff. Staff are all subject to medical confidentiality via their employment at the mental healthcare facility. Personally identifiable material, such as study consent forms, will be stored separately from research data files. Data will be stored for 20 years after completion of the trial. Data integrity will be supported by fully computerized procedures, i.e., participants answering all questionnaires via a computer or their smartphone (within the RoQua environment). Hence, the chance of data being recorded incorrectly is improbable.

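### Objective 2 compares the arms only among people who later enter HYPE, so randomisation does not protect the comparison, although the plan words it as an effect of PRIMARY

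*Protocol article*

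**What the plan says.** All references are to the Protocol article.

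- **Question and test** (Data analysis plan and power calculations). The aim is introduced as "Regarding the effect of PRIMARY on the effectiveness of subsequent specialized treatment (i.e., HYPE"). The test is stated as "an ANOVA-test repeated measures with a within-between interaction will be applied to Wave 1, 2 and 3", and the analysis set as "including only those participants receiving HYPE treatment (study objective 2".
- **Timing of entry** (HYPE). HYPE begins once the Wave 2 assessment is complete, and the article expects it for those with early-stage BPD, defined as three or more criteria.
- **Who decides** (HYPE). "Allocation to HYPE is determined by clinicians independent from the study".
- **What clinicians can see** (Design). "All individual participant data (i.e., questionnaires and weekly, graphical reports) are made available within the electronic patient record", and "this information can be integrated into their diagnostic or treatment process by their clinician". Data management repeats that "the answers on the questionnaires of this study are available to clinicians through these records".
- **What differs by arm** (Table 1 footnote). The ESM questionnaire, the source of the weekly reports, is completed in the intervention group only.
- **Who has Wave 3 data** (Measures). Only participants who enrol in HYPE.
- **Assurance given** (Data analysis plan and power calculations). For analyses of PRIMARY's effectiveness, the modified intention-to-treat set is said to secure random selection. No exception is made for objective 2.

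**The concern.** Randomisation makes the arms comparable in the set that was randomised, and in subsets defined by what was known beforehand. HYPE entry is neither. It follows the intervention, and two routes lead from arm to entry. First, PRIMARY is meant to improve self-harm and emotion regulation by Wave 2, just before HYPE starts, so it may change who still appears to need HYPE. Second, clinicians of intervention participants have weekly reports that clinicians of controls do not have.

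If either route operates, entrants in the two arms can differ already at Wave 1, and the group-by-time result mixes an effect of PRIMARY with selection into HYPE. A reader of the results would nevertheless take it as a randomised finding about PRIMARY followed by HYPE. Wave 3 is collected only in HYPE enrollees, so no Wave 3 analysis of everyone randomised could serve as a check.

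**Working it through.** **The plan's own figures.** The article puts no number on selection. Its sample size for objective 2 is 42 to 106 HYPE recipients, or 46 to 118 after 10% drop-out. With two groups, three waves and an assumed correlation of 0.5 between waves, the noncentrality is λ = f² × N × 3 / (1 − 0.5). N = 42 gives power 0.803 at f = 0.20, and N = 106 gives 0.807 at f = 0.125. These f values were found by search, because the text shown states none. The figures matter here only for scale: 46/180 = 26% and 118/180 = 66% of the planned sample, so the analysis set is a selected part of those randomised.

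**Illustration A: PRIMARY works, and both arms share one entry rule.** All inputs are assumptions: true Wave 2 effect 0.5 SD, Wave 1 to Wave 2 correlation 0.5, and entry that depends on Wave 2 severity.

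Let Z be a person's Wave 2 severity without PRIMARY (mean 0, SD 1). Observed Wave 2 severity is Z in controls and Z − 0.5 in the intervention arm. Expected Wave 1 severity is 0.5 × Z. Let m_C and m_I be the mean Z among entrants in each arm. Differences, intervention minus control:

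- Wave 1: 0.5 × (m_I − m_C)
- Wave 2: (m_I − m_C) − 0.5
- Change from Wave 1 to Wave 2: −0.5 + 0.5 × (m_I − m_C)

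Hard cut at the control median:

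- m_C = φ(0)/[1 − Φ(0)] = 0.3989/0.5 = 0.798
- m_I = φ(0.5)/[1 − Φ(0.5)] = 0.3521/0.3085 = 1.141
- m_I − m_C = 0.343

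For graded entry, the probability of entry is 1/(1 + exp(−b × Wave 2 severity)), and the means come from numerical integration.

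| Entry rule | Entry, control / intervention | m_C | m_I | Wave 1 gap (SD) | Change contrast (SD, true 0.50) | Lost |
|---|---|---|---|---|---|---|
| Logistic, b = 0.5 | 50% / 44% | 0.236 | 0.264 | 0.01 | 0.49 | 3% |
| Logistic, b = 1 | 50% / 40% | 0.413 | 0.500 | 0.04 | 0.46 | 9% |
| Logistic, b = 2 | 50% / 35% | 0.606 | 0.798 | 0.10 | 0.40 | 19% |
| Hard cut | 50% / 31% | 0.798 | 1.141 | 0.17 | 0.33 | 34% |

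For the hard cut, 0.5 − 0.5 × 0.343 = 0.328. Wave 3 is not modelled.

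**Illustration B: PRIMARY has no effect, but entry follows severity differently by arm.** This could happen if the reports give clinicians a clearer view of severity in one arm. Simulated rejection rates of the planned interaction test at α = 0.05, with a correlation of about 0.5 between waves and equal numbers of entrants per arm:

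| Logistic slope, intervention vs control | N = 42 | N = 106 |
|---|---|---|
| 1 vs 1 | 5.2% | 5.4% |
| 1.5 vs 0.5 | 7.1% | 11.6% |
| 2 vs 0.5 | 8.5% | 15.8% |
| 3 vs 0 | 18.8% | 44.2% |

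With slopes of 1.5 vs 0.5 and of 2 vs 0.5, about 50% of each arm enters HYPE. Equal entry rates therefore do not show that the entrants are comparable.

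**The case against.** The strongest defence is that the subset may in practice be fixed at baseline. The only entry criterion named is at least three BPD criteria, and Table 1 schedules the SCID-II BPD PQ at screening only, before randomisation. If entry followed that score alone, entrants would differ at Wave 1 only by chance. This limits the point to possible bias. It does not remove it, because the HYPE section only anticipates this route and leaves the decision to clinicians.

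Other parts of the defence also stand. The article says that clinicians can use the study data, not that these data drive HYPE decisions. The link between the questionnaire portal and the records is described for GGz Centraal, while the Design section states record availability generally. Apart from the ESM questionnaire and the evaluation of PRIMARY, the wave questionnaires are completed in both arms. With no PRIMARY effect and the same entry slope in both arms, the test keeps its 5% level.

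Three stronger readings are tempting and go too far:

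- **Selection removes half or more of the effect.** Under the hard cut, the Wave 2 difference alone is 0.16 SD, or 0.19 SD after regression on Wave 1 among entrants. The planned interaction contrasts change over time, however, and there the loss is about a third in that extreme case and 3% to 19% under graded selection.
- **The statement on clinician independence is false.** It says that the study does not make the decision. That can be true while clinicians read records whose content differs by arm.
- **The arms will differ at Wave 1.** They can differ; the documents do not establish that they will.

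**Conclusion.** The point holds as a limit on what objective 2 can claim. The between-arm comparison is made in a set formed after randomisation, by a decision that arm can influence. It is not protected by randomisation, and the assurance about random selection does not apply to it. Neither the size nor the direction of bias can be derived from the article. The figures above rest on assumed effects, correlations and entry rules, and show only that the distortion could range from negligible to material. The covariates named in the analysis section (age, gender, concomitant treatment) do not by themselves deal with selection into HYPE.

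A reader might infer that the trial's main result is compromised. The documents do not support that: objective 1 compares Waves 1 and 2 without conditioning on HYPE entry.

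**What to change.** 1. In the data analysis section, limit the statement on random selection to objective 1. Label the objective 2 between-arm comparison non-randomised and exploratory, and drop the causal wording.
2. Report HYPE entry, and the Wave 1 characteristics of entrants, by arm. Do this among all randomised and among those with at least three BPD criteria on the screening SCID-II BPD PQ. State that equal entry rates do not prove comparability.
3. Add a sensitivity analysis restricted to HYPE entrants who met that screening criterion, noting that this reduces selection but does not remove it. Inverse-probability weighting is optional, and only where entry probabilities overlap. Under a sharp entry threshold some people have no chance of entry and usable weights do not exist.
4. In the HYPE section, keep the statement about clinicians and qualify it: the study does not decide HYPE allocation, but clinicians may see study data that differ by arm.

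The cost is wording, one descriptive table and one sensitivity analysis on data already scheduled for collection, plus a more modest claim for objective 2. Clinical allocation does not change.
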